#### Anthropometrics

Child height is measured to the nearest 0.1 cm using a fixed stadiometer. Children are weighed to the nearest 0.1 kg wearing underwear. BMI is calculated based on weight and height. Waist circumference is measured to the nearest 0.1 cm at the midpoint between the lower rib and the iliac crest using a non-extensible tape. Systolic and diastolic blood pressure is measured using an automatic blood pressure monitor. Each measure is performed three times and mean values are then calculated. For all children anthropometrics are measured in a standardized manner by trained health care professionals with calibrated instruments.

#### Metabolic markers and blood pressure

Fasting blood samples are collected at baseline and at 12 months and taken at the family’s local primary health care facility. The metabolic markers examined are: P-glucose, B- HbA1c, P-cholesterol, P- LDL-cholesterol, P-HDL-cholesterol, P-triglycerides, P-ALAT, P-ASAT, P-urate, S-TSH, P-CRP and S-insulin. These metabolic markers are recommended for annual tests in pediatric obese patients.

#### Child food and physical activity habits

Dietary intake is assessed by a short version of an established food frequency questionnaire. To assess eating patterns, additional questions included: the child’s breakfast habits, who is responsible for the child’s food and physical activity and peer influence on the child’s food and physical activity. The questions regarding the child’s sedentary behavior focused on child screen time during weekdays and weekends.

The instruments used to measure child and parental behaviors are presented in Table 3 and briefly described below.

**Table 3 Tab3:** Measures used in the study

Name of Instrument	Reference	Domains measured	Number of items	Brief description of measures:
Child Eating Behavior Questionnaire (CEBQ)	Wardle et. al. 2001		35	
		*Food Approach*		
		Food Responsiveness (FR)	5	The child’s general appetite.
		Enjoyment of Food (EF)	4	The child’s interest in food.
		Emotional Overeating (EOE)	4	If the child eats as a response to emotions.
		Desire to Drink (DD)	3	The child’s desire to drink
		*Food Avoidance*		
		Satiety Responsiveness (SR)	5	If the child gets full easily or not.
		Slowness in Eating (SE)	4	The child's speed of eating.
		Emotional Undereating (EUE)	4	If the child eats less as a response to emotions.
		Fussiness (FU)	6	The child eats a limited variety of food.
Lifestyle Behavior Checklist (LBC)	West and Sanders 2009 West et. al. 2010	Problem Scale/Confidence Scale	25	Parent’s perceptions of child obesity related problem behavior. Parent’s confidence in handling problematic behaviors.
		Overeating (OE)	7	If the child eats large potions or often asks for food.
		Misbehavior in relation to food (MB)	7	If the child throws tantrums about food or gets angry if not given food.
		Emotional correlates of being overweight (EMO)	5	If the child complains about e.g. peer problems, clothes being too small.
		Physical Activity (PA)	5	If the child is reluctant to physical activity and engages in sedentary behaviors.
Child Feeding Questionnaire (CFQ)	Birch et. al 2001			
		Perceived Responsibility (PR)	3	Parental perception of their responsibility for child feeding.
		Parent Perceived Weight (PPW)	4	Parental perception of their own weight status history.
		Perceived Child Weight (PCW)	6	Parental perception of child weight status history.
		Concern about child weight (CN)	3	Parental concern about the child’s risk of overweight.
		Monitoring (MN)	3	The extent to which parent’s oversee the child’s food intake.
		Restriction (RST)	8	The extent to which parents restrict the child’s access to food.
		Pressure to Eat (PE)	4	Parent’s tendency to pressure the child to eat more food.
Family Assessment Device (FAD)	Epstein et. al. 1983			
		Problem Solving	5	Ability to resolve problems in the family.
		Communication	6	Exchange of clear and direct verbal information.
		Roles	8	Division of responsibility for completing family tasks.
		Affective Responsiveness	6	Ability to respond with appropriate emotion
		Affective Involvement	7	Degree to which family members are involved and interested in one another.
		Behavior Control	9	Manner used to express and maintain standards of behavior.
		General Functioning	12	Overall function in the family.
Child Behavior Checklist (CBCL)	Achenbach and Rescorla 2000		99	
		*Internalizing Scale*		
		Emotionally Reactive	9	The child is easily disturbed, has mood swings etc.
		Anxious/Depressed	8	The child is overly sensitive, clings to parent or too independent, sad etc.
		Somatic Complaints	11	The child has aches, pain or vomits with no medical reason etc.
		Withdrawn	8	The child shows little interest in people or surroundings, doesn’t answer etc.
		Sleep Problems (not included in the Internalizing Scale)	7	The child doesn’t want to sleep alone, has nightmares, has little sleep etc.
		*Externalizing Scale*		
		Attention Problems	5	The child can’t concentrate or sit still, wanders away et.
		Aggressive behavior	19	The child is angry, defiant, disobedient, demanding, stubborn etc.
Beck’s Depression Inventory II (BDI-II)	Beck et. al 1988	Mood, Pessimism, Sense of Failure, Lack of Satisfaction, Guilt Feelings, Sense of Punishment, Self-dislike, Self-accusation, Suicidal Wishes, Crying, Irritability, Social Withdrawal, Indecisiveness, Distortion of Body Image, Work Inhibition, Sleep Disturbance, Fatigability, Loss of Appetite, Weight Loss, Somatic Preoccupation and Loss of Libido.	21	Symptoms and attitudes to assess intensity of depression.
Communicating with Children	(self-developed)		12	
		Limit Setting Strategies		Parents limit setting strategies (consequent or not)
		Emotional Regulation		Parents ability of emotional control

#### Child obesity related behavior

The Child Eating Behavior Questionnaire (CEBQ) includes 35 items on eating styles related to obesity risk, measured on eight factors [79]. The first four factors represent the dimension ‘food approach’ and the other four factors represent ‘food avoidance.’ Parents rate each behavior on a five-point Likert scale (never, rarely, sometimes, often, always; 1–5). The CEBQ has proved to have a good validity and high internal reliability in several studies [79, 98–103].

The Lifestyle Behavior Checklist includes 25 items divided on two scales: the Problem scale and the Confidence scale. On the Problem scale, parents rate to what extent an obesity related behavior is a problem for them with their child, from 1 (not at all) to 7 (very much). On the Confidence scale, parents rate how confident they are in dealing with the problematic behaviors, from 1 (Certain I can’t do it) to 10 (Certain I can do it) [24]. The factor structure was explored in a separate study presenting four factors [104], presented in Table 2. The LBC was developed in Australia and has been validated in the Netherlands [22]. In both countries the instrument has successfully been able to discriminate between healthy weight children and children with overweight/obesity [22, 24] and showed sensitivity to changes after an obesity treatment program [26]. To be able to assess changes in child behavior and parental confidence in the ML we have translated and validated the LBC in a separate study. The LBC was tested in a large Swedish preschool population regarding factor structure, construct validity, internal reliability (Cronbach’s alpha) and discriminative validity [23].

#### Child behavior problems

Child psychosocial health and functioning will be assessed with the Child Behavior Check List for Ages 1.5–5.5 (CBCL/1.5–5.5) that includes 99 questions representing seven syndromes clustering on seven factors. The first four cluster on the Internalizing scale and the last two on the Externalizing scale [105]. The parents rate each behavior from: 0- not true, 1- somewhat or sometimes true and 2- very true or often true. The psychometric properties of the CBCL/1.5–5.5 have been tested for generalizability across 23 countries, including Scandinavian countries. In this large study, including over 19 000 preschool aged children, the CBCL proved to be valid and reliable to measure for emotional, behavioral and social problems in children in different cultures [106]. The CBCL has also been validated in Sweden on a preschool population [107].

#### Parenting practices

Parental feeding practices will be measured with the Child Feeding Questionnaire (CFQ). CFQ consists of 31 items and assesses parents' perceptions and concerns about child obesity, as well as their child-feeding attitudes and practices [108]. The instrument is well suited for use in research concerning parents of preschool-aged children [109]. The CFQ consists of seven factors; the first four factors measure parents’ perceptions of their own and their child’s weight at different ages, and concerns parents may have that can affect how they control their child’s eating; the last three factors measure parental attitudes and feeding practices [108]. In a Swedish validation study the CFQ proved to be a valid and reliable measure in a preschool population after few adjustments [92].

To assess general parenting practices we have developed a questionnaire, Communicating with Children (CC), measuring parents’ limit setting strategies (are they consequent or not) and emotional regulation (are the parents able to control negative emotions when communicating with the child in different situations). Limit setting and emotional regulation are two important aspects discussed and practiced during the parent group sessions. The factor structure, internal reliability, construct validity and discriminative validity will be assessed in a separate study based on the same Swedish preschool population as the one used for validating the LBC, described above.

Parents’ confidence in handling child problematic obesity related behaviors will be measured with the LBC, see above [24].

#### Family function and parental depression

Family functioning will be assessed with the Family Assessment Device (FAD) consisting of 60 items loading on seven factors [110–112]. The instrument has proved to be a reliable tool and can provide valid assessments in a wide range of families [112].

Parental level of depression will be assessed with the Beck Depression Inventory II (BDI-II) [113]. The BDI-II consists of items regarding 21 symptoms and attitudes rated on a 4 point Likert scale from 0 to 3 during the past week. The BDI-II is a commonly used instrument with good psychometric properties proved in many studies on both clinical and non-clinical populations [113].

### Statistical analysis

We will use descriptive statistics (e.g., means, medians, percentages and frequencies) to describe demographic and other subject characteristics and evaluate variable distributions with histograms and boxplots. We will employ several multivariate analytic strategies, including Multi Analysis of Variance (MANOVA), multiple regressions, and structural equation modeling (SEM) controlling for baseline and other covariates. To maximize our multimethod, multiagent approach, we will use the SEM framework most often.

For our analyses we will use SPSS Statistics 23 (IBM, Armonk, NY, USA) and Mplus 7 (Muthen & Muthen. Los Angeles, CA). The advantages of Mplus is that it allows for regression among and between random effects and factors and employs full information maximum likelihood (FIML) estimation to allow for missing data or data that are missing at random (MAR). Even when the MAR assumption is not met, FIML produces less biased estimates than list wise deletion. This feature is particularly advantageous when dealing with longitudinal data.

Latent growth model (LGM) will be used to test intervention effects of the two treatment approaches on decreased BMI SDS. LGM is a preferred method for testing changes in outcome measures in clinical research because it allows for the estimation of average trajectories (mean intercepts and slopes) and individual differences in these trajectories (intercept and slope variances); repeated measures ANOVAs allow for the estimation of mean growth patterns only [114].

Below we describe specific examples of the analyses that will be conducted to test our aims. In Fig. 3 (Specific Aim 1) we illustrate a LGM where child BMI SDS is modeled as a function of two latent variables, an initial status or intercept factor (representing BMI SDS at baseline) and a slope factor (representing the magnitude of change in BMI SDS over the course of the study). A negative mean for the slope factor in this model would indicate a significant intervention effect on child BMI SDS. For the simplicity of the presentation, the example includes only treatment status as a predictor. However, this model will be expanded to include other hypothesized predictors (e.g., child weight status, parental depression, and SES).

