### The power calculation

The power calculation was based on data from Kleber et al. [7]. We hypothesize that standard treatment will be slightly less effective than the intensive treatment obtained in the German study (we assume -0.3 BMI SDS compared to -0.46). We expect a dropout rate of 21 % based on the Australian study by West and colleagues with similar design but older children [26]. We hypothesize that the parent group treatment will be twice as good as standard treatment with regard to the primary outcome BMI SDS (i.e., -0.6 one year post baseline). The calculation is based on pairwise/three group comparisons. Based on these assumptions we will require at least 75 children in each group (*p* < 0.05 and power 85 %) to be able to detect changes between two groups; standard treatment and parent group treatment (primary outcome).

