#### Parent group treatment

In a close collaboration with the KEEP developers we translated and adapted the parent group manual outlining the content of each session and parent handouts. The standard 16-session program was shortened to a 10-session program, 1.5 h per week, for Swedish parents with preschoolers with obesity following cultural adaptation (especially for limit setting strategies). Furthermore, new parent material containing tailored advice on food and physical activity was developed.

Each session centers around a parenting practice that is presented, discussed and practiced. See Table 1 for a description of session content. Each session also includes a lifestyle component (regarding food and physical activity/sedentary behaviors) aimed to provide parents with knowledge and skills to support a healthy home environment. The sessions finish with a home practice assignment related to the focus of the day. Two group leaders (one group leader and one co-leader) with health care backgrounds facilitate the sessions that consist of 6–10 parents. Both parents are invited and child care is provided. All sessions are videotaped and analyzed with respect to program fidelity and program improvements [96].

**Table 1 Tab1:** Content description of the parent group program

Session	
1.	Welcome and Introduction: Parents’ Key Roles
2.	Food and Play: When More, When Less?
3.	Cooperation
4.	Parents as Teachers
5.	Charts and Incentives
6.	Pre-teaching and Planning
7.	Limit Setting Strategies
8.	Power Struggles
9.	More Support – Less Stress
10.	Summary: Parenting and Balancing Food and Play

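### Neither the stated sample size nor the Aim 1 growth model allows for clustering by parent group; if outcomes correlate within groups, the parent-group versus standard test is anti-conservative

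*Protocol article*

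**What the plan says.** Under Parent group treatment, two leaders "facilitate the sessions that consist of 6–10 parents", weekly for ten weeks. Both parents of a child are invited. Under Standard treatment, each family is seen by a physician and nurse in an outpatient pediatric unit.

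Under The power calculation, the article assumes a standard-treatment change of −0.3 BMI SDS ("we assume -0.3 BMI SDS compared to -0.46", the second figure being that of the German cohort used as the source). The parent-group change is twice that, minus "0.6 one year post baseline". With 21% dropout and "< 0.05 and power 85"%, the conclusion is that "we will require at least 75 children in each group". No SD, ICC, design effect or treatment-group size is given.

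Under Statistical analysis, the primary method is stated: "Latent growth model (LGM) will be used to test intervention effects of the two treatment approaches on decreased BMI SDS". The model has an intercept factor and a slope factor for each child, with treatment status as predictor. The planned expansions are further predictors such as parental depression and SES. No group level is named.

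Under Allocation, families and leaders do not learn who will receive boosters until the groups have ended.

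**The concern.** Families in one parent group share leaders, peers, discussion and role play for ten weeks, and the article describes these as the active parts of the programme. Under Lack of blinding it adds that the staff who run the groups also measure these children. Both are reasons to expect BMI SDS changes to be somewhat alike within a group.

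Standard-treatment families have no such grouping, so the trial is partially nested. Aim 1, the primary comparison, is the contrast between the grouped and the ungrouped half. A child-level slope variance does not stand in for a group effect, because it still treats two children from the same group as independent. If the ICC is positive, the model as described gives the primary contrast too small a standard error, too narrow a confidence interval and too small a p-value.

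**Working it through.** **Inputs from the article.** Difference 0.6 − 0.3 = 0.3 BMI SDS; alpha 0.05 (taken as two-sided, since sidedness is not stated); power 85%; 75 per group; dropout 21%; 90 randomized per approach.

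**Assumptions, because the article gives no figure.** ICC of the one-year change, 0 to 0.10. Children per group m, 3 to 10: sessions hold 6–10 parents and both may attend, so 6 parents could be 3 children and 10 parents could be 10 children. Standard-treatment children are taken as independent, and total variance as equal in the two approaches.

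**1. The plan's own figure.** Without an SD, 75 cannot be reproduced. It can only be solved backwards:

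SD = 0.3 × √(n/2) / (1.960 + 1.036)

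- 75 read as completers: 0.3 × √37.5 / 2.996 = 0.613.
- 75 read as already including dropout (75 × 0.79 = 59.25 completers): 0.3 × √29.625 / 2.996 = 0.545.

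A one-sided test would imply 0.685, and a three-way split of alpha 0.536. The article does not settle which applies.

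**2. Variance of the Aim 1 contrast.** Clustering acts in one approach only:

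DEFF = 1 + (m − 1) × ICC; variance ratio V = (1 + DEFF)/2

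True two-sided error of the test that ignores groups = 2 × [1 − Φ(1.96/√V)]

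Example, m = 8 and ICC 0.05: DEFF = 1.35, V = 1.175, √V = 1.084, 1.96/1.084 = 1.808, error 7.1%.

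| Children per group | ICC 0 | 0.01 | 0.05 | 0.10 |
|---|---|---|---|---|
| 3 | 5.0% | 5.1% | 5.6% | 6.2% |
| 5 | 5.0% | 5.2% | 6.2% | 7.4% |
| 8 | 5.0% | 5.4% | 7.1% | 9.2% |
| 10 | 5.0% | 5.5% | 7.7% | 10.4% |

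A null simulation of 90 versus 90 children (40,000 runs, t-test) agrees. At ICC 0, 0.05 and 0.10 it gives 5.0%, 7.0% and 9.1% for m = 8, and 5.0%, 6.2% and 7.2% for m = 5.

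**3. Booster versus no booster.** Because boosters are disclosed only after the groups end, the two allocations appear to share groups. In the same simulation, with allocations balanced within groups of 8, the test that ignores groups rejects in 4.4% (ICC 0.05) and 4.0% (ICC 0.10) of runs. With simple randomization across groups it stays near 5%.

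**4. Power for Aim 1.** Completers per approach: 90 × 0.79 = 71.

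Power = Φ(0.3 / [SD × √((1 + DEFF)/71)] − 1.96)

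| SD | No clustering | ICC 0.05, m = 5 | ICC 0.05, m = 8 | ICC 0.10, m = 5 | ICC 0.10, m = 8 |
|---|---|---|---|---|---|
| 0.613 | 83% | 79% | 77% | 76% | 71% |
| 0.545 | 91% | 88% | 86% | 85% | 81% |

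In the first row, the 2 points from 85% to 83% come from having 71 rather than 75 completers, not from clustering. Dropout would also shrink the groups, so m is somewhat smaller among completers.

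**The case against.** The strongest reply is that independence is being inferred from silence. The article nowhere says that children are treated as independent. It presents its models as simplified examples, it uses software that can fit clustered models, and the full protocol and analysis plan are not shown. That stands as a limit on wording: one cannot say the trial will ignore clustering, only that the article states no allowance for it. It does not remove the point. The sample size is given as a finished result, the Aim 1 model is described down to its two factors, and the expansions named are covariates. The remark that Mplus handles random effects describes the software and not a planned term.

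Three stronger readings are tempting, and the documents do not support them.

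- A reader might infer that type I error definitely exceeds 5%. That depends on an ICC the article does not give: at 0 there is no excess, and at 0.01 at most about half a percentage point. Groups are also counted in parents, so as few as 3 children may share one.
- A reader might infer that the 85% power is overstated. That holds if 75 means completers, but if 75 already includes dropout, power at ICC 0.05 with 5–8 children per group is still 86–88%.
- A reader might extend the inflation to the booster comparison. If those families share groups, that test is about nominal or slightly conservative.

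**Conclusion.** The point holds for Aim 1 in conditional form. Treatment is grouped in one approach and not in the other, and neither the stated sample size nor the described growth model reflects this. For any positive ICC the Aim 1 test is anti-conservative. Since the excess arises in the test that would declare the parent programme superior, it weakens any such claim.

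The size is modest at small ICCs (under 3 percentage points at 0.05) and reaches about 5 points only at ICC 0.10 with 10 children per group. These figures rest on assumed ICCs and group sizes, and on a simple comparison of change standing in for the growth-model slope. A power shortfall is possible but not shown. The missing SD, which leaves 75 unverifiable, is a separate matter.

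**What to change.** Record the parent-group identifier for every family in the parent-group arms. Leaders already complete weekly attendance forms, so membership should be known.

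Fit the Aim 1 comparison with a group-level random effect on change (the slope) in the parent-group arms only, with each standard-treatment child as its own singleton. Use small-sample degrees of freedom, because there will be few groups: 90/8 ≈ 11 to 90/5 = 18 at 5–8 children each. The mixed-model procedure in SPSS can do this, and a two-level or cluster-robust run in Mplus can serve as a check. Keep the group effect in the booster comparison, where groups appear to contain both allocations.

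Restate the power calculation with the SD, ICC and children per group shown as assumptions with ranges, and say whether 75 is before or after dropout.

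The cost is in analysis wording and one recorded variable. The downside is a slightly wider interval for the primary comparison and possibly a less favourable stated power.

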**Methods/design:**

This is a parallel open label randomized controlled trial assessing two different behavioral treatment approaches offered in three conditions to families with children aged 4–6 years in Stockholm County, Sweden. Children (n = 180) identified as obese will be referred from primary child health care, school health care, and from outpatient pediatric clinics, and randomized to: 1) a standard treatment with focus on lifestyle, provided within the current healthcare system (n = 90); 2) a 10-session, 1.5 h/week group treatment with focus on parenting (n = 45); or 3) the same group treatment as 2) with additional follow-up sessions (n = 45). The primary study outcome is change in children’s body mass index standard deviation score (BMI SDS) one year post-baseline. Secondary outcomes include changes in children’s waist circumference, metabolic health, lifestyle patterns (Food Frequency Questionnaire), obesity-related child behaviors (Child Eating Behavior Questionnaire and Lifestyle Behavior Checklist, Problem Scale), parents’ general and feeding parenting practices (Communicating with Children and Child Feeding Questionnaire) and lifestyle-specific self-efficacy (Lifestyle Behavior Checklist, Confidence Scale), family functioning (Family Assessment Device), child and parental psychosocial health (Child Behavior Checklist and Beck’s Depression Inventory II).

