**Fig. 4 Fig4:**
[figure not shown]
Structural Equation Modeling testing mediating effects of parenting and home environment on BMI SDS

We expect that treatment effect on child BMI SDS will vary depending on socio-economic and demographic factors. Fig.5 illustrates how we will examine the moderating effects of socio-economic and demographic factors using parental depression as an example (Specific Aim 3). We expect that children with parents experiencing higher levels of depression will have a higher BMI SDS at 12 months post-baseline compared to the children whose parents experienced lower levels of depression.

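### The criterion stated for the primary latent growth model is the wrong parameter: a negative slope mean shows change over time, and only the treatment coefficient on the slope compares the arms

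*Protocol article*

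**What the plan says.** The abstract defines the endpoint: "The primary study outcome is change in children’s body mass index standard deviation score (BMI SDS) one year post-baseline". The Statistical analysis section names the method: "Latent growth model (LGM) will be used to test intervention effects of the two treatment approaches on decreased BMI SDS".

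It then describes the example for Specific Aim 1 (Fig. 3). BMI SDS depends on two latent variables: an intercept factor for baseline status and "a slope factor (representing the magnitude of change in BMI SDS over the course of the study"). The criterion follows directly: "A negative mean for the slope factor in this model would indicate a significant intervention effect on child BMI SDS". The next sentence says that, for simplicity, "the example includes only treatment status as a predictor".

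Two other places matter. The power calculation fixes the primary contrast, with a sample size chosen "to be able to detect changes between two groups; standard treatment and parent group treatment (primary outcome"). It also expects improvement under standard treatment: "we assume -0.3 BMI SDS compared to -0.46", the second figure being the result of the German cohort on which it draws. The parent group is expected to reach -0.6. The limitations (Lack of non-treated control group) confirm that every child is offered active treatment.

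**The concern.** In a growth model with treatment status as a predictor, the slope factor has two parameters that must be kept apart.

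- **Its mean or intercept.** With 0/1 coding this is the change in the reference arm. With centred coding, or as an overall model-implied mean, it is the average change across children.
- **The coefficient of treatment status on the slope.** This is the difference in change between the arms.

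The article attaches the intervention effect to the first of these. It also treats a negative value as if it were a significant one.

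If the sentence were followed as written, improvement from standard care, from natural change in BMI SDS or from regression to the mean would count as support for the parent group programme. The same reading would count a trial in which the parent group did worse than standard treatment as a success, provided that children improved on average.

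**Working it through.** **Inputs from the article.** Change of -0.3 under standard treatment and -0.6 under the parent group; at least 75 per group, p < 0.05, power 85 %; dropout 21 % (all from The power calculation). Allocation 2:1:1 of 180, that is 90 against 45 + 45. Visits at 0, 3, 6 and 12 months.

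**Completers.** 90 × 0.79 = 71.1, so 71 per approach; 180 × 0.79 = 142.2, so 142 in all.

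**The plan's own figure.** No SD is stated, so the 75 per group can be neither confirmed nor refuted. It can be solved backwards for the SD with SD = 0.3 / [(z_α + z_0.85) × √(2/n)]:

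- 75 evaluable, two-sided: 0.3 / [(1.960 + 1.036) × √(2/75)] = 0.613.
- 75 including dropout (75 × 0.79 = 59.25 evaluable), two-sided: 0.545.
- The same two cases one-sided: 0.685 and 0.609.

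The article is therefore consistent with an SD of 0.545 to 0.685. I also show 0.4 to 1.0 as a wider assumed range.

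**Chance of a significantly negative slope mean when the arms do not differ.** Put both arms at -0.3. By normal approximation P = Φ(0.3 × √N / SD − 1.96). For N = 142 the numerator is 0.3 × 11.916 = 3.575; for N = 71 it is 0.3 × 8.426 = 2.528.

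| SD (assumed) | Pooled mean, N = 142 | Reference arm, N = 71 |
|---|---|---|
| 0.4 | Φ(6.98), > 0.999 | Φ(4.36), > 0.999 |
| 0.545 | Φ(4.60), > 0.999 | Φ(2.68) = 0.996 |
| 0.613 | Φ(3.87), > 0.999 | Φ(2.16) = 0.985 |
| 0.685 | Φ(3.26) = 0.999 | Φ(1.73) = 0.958 |
| 0.8 | Φ(2.51) = 0.994 | Φ(1.20) = 0.885 |
| 1.0 | Φ(1.61) = 0.947 | Φ(0.57) = 0.715 |

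A valid two-sided 5 % test would favour the parent group in 2.5 % of such trials. If the common change were only -0.1, the pooled probability would still be 0.22 (SD 1.0) to 0.85 (SD 0.4).

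**Simulation.** 20,000 trials per scenario, 71 per arm, the four planned visits, a random intercept and slope, and complete data. Assumed: SD of 12-month change 0.613 and residual SD 0.2. The pooled slope mean is compared with the between-arm difference in slope, which is the treatment coefficient.

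| True change: standard, parent group | Slope mean significantly negative | Treatment coefficient significant, two-sided |
|---|---|---|
| -0.3, -0.3 (no difference) | 99.995 % | 5.4 % |
| -0.3, -0.6 (as planned) | 100 % | 83 % |
| -0.6, -0.3 (parent group worse) | 100 % | 83 %, against the parent group |
| 0, 0 (no change at all) | 2.7 % | 4.9 % |

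Of these scenarios, the slope mean keeps its nominal level only in the last, where neither arm changes. The plan's own assumption of -0.3 under standard treatment excludes that case. On sign alone, without any test, the slope mean was negative in 100 % of the simulated trials with both arms at -0.3, and in 49.7 % of those with no change at all.

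**The case against.** The strongest defence is that the sentence is loose shorthand. The section introduces its models as examples. Treatment status is a predictor in this one, the section says that the model tests the effects of the two approaches, and both the power calculation and the hypothesis are framed against standard treatment. Fig. 3, which may show the path from treatment to slope, is not shown in the text at hand. The authors may well have meant that path.

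This stands as a limit on the finding. A reader might infer that the trial will not test its comparative question. The documents do not support that, because the predictor needed for the test is in the model and the fitted analysis may be correct. But the defence does not make the sentence true. With only an intercept factor and a slope factor, no coding of treatment turns the slope mean into a contrast. The example is also tied to Specific Aim 1 and the primary outcome.

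A reader might also infer that the moderation analysis has the same fault, because the text after Fig. 4 says: "We expect that children with parents experiencing higher levels of depression will have a higher BMI SDS at 12 months post-baseline". Taken alone, that is a prognostic statement. But it is worded as an expectation and not as a test, the same paragraph opens by saying that the treatment effect should vary with such factors, and the model itself is in Fig. 5, which is not shown. Whether it has an interaction term cannot be judged, so no fault is claimed there.

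Finally, the probabilities rest on an SD that the article does not give. That is correct, and it is why a range is shown. That the slope mean is the wrong parameter does not depend on the SD.

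**Conclusion.** The criterion is wrong as written. It identifies the intervention effect with the slope mean, when the treatment comparison is the coefficient of treatment status on the slope, and it reads a negative sign as significance.

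Under the article's expectation of -0.3 for standard treatment, and with no difference between arms, the pooled mean would be significantly negative with probability about 0.95 to above 0.999. For the reference arm alone the figure is about 0.96 to above 0.99 at the back-solved SDs of 0.545 to 0.685, and about 0.72 at SD 1.0. These figures assume 142 and 71 completers, an SD of 12-month change in the stated ranges, and a normal approximation.

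The conclusion covers the written criterion for the primary model only. It does not extend to the fitted model, which cannot be seen, or to the moderation analysis.

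**What to change.** Replace the sentence in the Statistical analysis section with:

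> A negative, statistically significant coefficient of treatment status (parent group vs standard treatment) on the slope factor would indicate an intervention effect on child BMI SDS; the slope mean describes change over time and does not compare the treatments.

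Check that Fig. 3 and its legend agree with this wording. Sidedness, interval reporting and similar detail can stay in the analysis plan. The cost is one sentence: the treatment predictor is already in the described model, and no data, visits or participants are added.
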